#### Primary analysis

Primary analysis will be of log-transformed AUC of 7 day CRP. The primary analysis will include all patients with at least 4 follow-up readings, on an intention-to-treat basis, and a secondary analysis will include only those with all follow-up readings on a per-protocol basis. ANOVA (analysis of variance) will be used to analyse the primary outcome measure and to estimate the treatment effect. For patients with at least 4 readings, any missing measurements will be imputed using the last observation carried forward method. After adjustment for the interim analyses, based on the method of O'Brien and Fleming, the primary endpoint will be considered to be statistically significant if it shows a treatment effect equivalent to p < 0.045.

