### Randomisation

Randomisation will be performed using a 24-hour voice interactive system set up the trial co-ordinating centre (Clinical Trials and Evaluation Unit (CTEU) of the Royal Brompton Hospital, London). Centres will be asked for a few simple details about the patient including initials, date of birth and eligibility criteria. The caller will be given a randomisation number, corresponding to blinded study treatment, and a fax or e mail will be sent to the centre confirming this. Randomisation will be stratified by centre and by whether glycoprotein IIb/IIIa antagonists are being used or planned. Patients entered into the study in this way will be considered as part of the intention to treat cohort irrespective of whether they actually receive treatment or not, or if they subsequently with draw from the study.

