### Study related investigations and follow-up

Patients will have blood taken every day for seven days for hsCRP (baseline and days 1–7, 14 and 30), Troponin (baseline and days 1–7 and 14), full blood count (baseline, days 7 and 14), creatinine, electrolytes, liver function tests (baseline, days 1–7 and 14), Interleukin-6 and von Willebrand factor (baseline, days 1–3,14,30). Blood will be taken prior to administration of either IL-1ra or placebo. A summary of samples and study related procedures to be undertaken is shown in Table 1. If the patient is discharged before the seventh day, they will be required to attend clinic to have the remaining blood samples taken.

**Table 1 T1:** Study procedures

Procedure	Baseline	Days 1 – 7	Days 8–13	Day 14	Day 30 (end of study)
Clinical evaluation	√	√		√	√
Informed consent	√				
Randomisation	√				
ECG	√	√		√	
Study drug given		√	√	√	
Full blood count	√	√		√	
Creatinine, electrolytes, eGFR	√	√		√	
Troponin	√	√		√	
hsCRP	√	√		√	√
Liver function tests	√			√	
IL-6, vWF	√	√		√	√
Post discharge follow up visit				√	√
Samples for DNA & RNA	√				√
Cardiac magnetic resonance scan (1)		√			√
ST segment monitoring (2)		√			
Forearm endothelial study (3)		√		√	

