### Statistics

#### Sample size

To provide the study with an 80% power to detect a relative reduction of one-third (the reduction seen in IL-1ra treatment of rheumatoid arthritis at this dose (data on file [Amgen]) between the treatment and the placebo groups at a 5% level of significance will require approximately 80 patients in each group (total 160). This is based upon the log-transformed value of the area under the curve and a standardised difference (difference/standard deviation [D]) of approximately 0.45. The standardised difference had been used since it is very difficult to estimate what the values of the log-transformed AUC will be. A change of 0.45 on the standardised normal will correspond to a one-third change in the primary outcome, regardless of the scale of the measurement, assuming the outcome measure is normally distributed. As the sample size is sufficiently powered to detect a change equivalent to one-third on the standard normal, it will also be sufficient to detect the same level of change on the primary outcome measure. It is anticipated that follow-up will be near complete in this study. However, allowing for data loss, for whatever reason, of 10% in each arm we have increased the required sample size to approximately 180 patients (60/centre). Furthermore, the sample size needs to be adjusted for the 2 interim analyses that will be conducted during the trial. Using the method of O'Brien and Flemming (1979) gives an increased sample size of 184 patients.).

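### The primary ANOVA of log hsCRP AUC names no baseline covariate and does not say whether the stratification factors are in the model, so precision available at no cost is not secured

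*Protocol article*

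**What the plan says.** Four sections of the protocol article bear on this point.

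- **Primary analysis.** The variable is fixed: "Primary analysis will be of log-transformed AUC of 7 day CRP". So is the method: "ANOVA (analysis of variance) will be used to analyse the primary outcome measure and to estimate the treatment effect". No model term other than treatment is mentioned.
- **Study related investigations and follow-up.** hsCRP is measured at baseline, on days 1 to 7, and on days 14 and 30. On timing the section says: "Blood will be taken prior to administration of either IL-1ra or placebo". A pre-treatment value of the outcome marker is therefore scheduled for every patient.
- **Randomisation.** "Randomisation will be stratified by centre and by whether glycoprotein IIb/IIIa antagonists are being used or planned".
- **Sample size.** The target of about 80 per group rests on a two-group standardised difference: "This is based upon the log-transformed value of the area under the curve and a standardised difference (difference/standard deviation [D]) of approximately 0.45". No reduction in variance for a baseline covariate is taken.

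**The concern.** A continuous baseline term would turn the named method into an analysis of covariance. Read plainly, then, the stated method leaves baseline hsCRP out, and the sample size fits that reading. If the pre-dose value predicts the 7-day AUC, leaving it out makes the confidence interval wider and the power lower than the same patients and samples could give.

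There is some reason to expect a relation. The marker is the same, and patients may enter at any time up to 48 hours after symptom onset, so starting levels are likely to differ. The remark in the Background section (Markers of inflammation in ACS) that no baseline level exists for comparison is an objection to percentage change as a measure. It does not argue against using the pre-dose value as a covariate.

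The strata raise a separate question of specification. Factors used to balance the randomisation are normally carried in the model. If they predict the outcome and are left out, the standard error is too large. The text does not settle whether they are in.

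**Working it through.** **1. Reproduce the plan's figure.** Inputs from the Sample size section: standardised difference 0.45, power 80%, alpha 5% (taken as two-sided, which the text does not state).

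n per arm = 2 × (1.960 + 0.842)² / 0.45² = 77.5, so 78 per arm (79 with the t distribution). The plan's figure of about 80 per group is reproduced by a plain two-group comparison with no covariate.

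**2. Base case at the final analysis.** The plan arrives at 184 patients after allowing for 10% data loss and the interim looks. Evaluable: 184 × 0.9 = 165.6, about 166, or 83 per arm. The final threshold in the Primary analysis section is p < 0.045. The noncentral t distribution with noncentrality 0.45 × √(83/2) = 2.90 gives power of 81.0%. The target of 80% is met without adjustment.

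**3. Add log baseline hsCRP.** With correlation r between log baseline hsCRP and log AUC, residual variance falls by the factor 1 − r². Then:

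- effective standardised difference = 0.45 / √(1 − r²)
- equivalent unadjusted evaluable total = 166 / (1 − r²)

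The document gives no value of r, so a range is assumed. The few degrees of freedom spent on covariates are ignored.

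| r (assumed) | 1 − r² | Effective difference | Power (83 per arm, alpha 0.045) | Equivalent unadjusted total |
|---|---|---|---|---|
| 0 | 1.00 | 0.450 | 81.0% | 166 |
| 0.2 | 0.96 | 0.459 | 82.5% | 173 |
| 0.3 | 0.91 | 0.472 | 84.5% | 182 |
| 0.5 | 0.75 | 0.520 | 90.7% | 221 |
| 0.7 | 0.51 | 0.630 | 97.9% | 325 |

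The confidence interval narrows by the factor √(1 − r²): about 2%, 5%, 13% and 29% for the four non-zero values of r.

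**4. Add the strata alone.** This step uses the plan's 80 per arm, alpha 0.05 and the normal approximation, for which unadjusted power is 81.2%. If centre and GP IIb/IIIa use explained 5% or 10% of the variance (assumed), power with both in the model would be 83.2% or 85.1%. If the arms are balanced within strata and the strata are left out, the true type I error is 2 × [1 − Φ(1.960 / √(1 − R²))] = 0.044 or 0.039 against a nominal 0.05. Omission therefore makes the test conservative.

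**The case against.** The strongest reply is that nothing here is invalid. A two-group ANOVA of log AUC in a randomised trial is unbiased, the sample size was computed for that comparison, and the planned power is reached. A chance imbalance in starting CRP does move a single estimate, but the unadjusted standard error already allows for it. All of this stands, and it limits the point to one of efficiency.

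A reader might also infer that the trial ignores its own strata, or that it commits to an unadjusted model. The document does not support either reading. It never calls the ANOVA unadjusted or one-way. ANOVA can carry categorical factors, and both strata are categorical. Model terms are often left to an analysis plan, which is not shown. All that can be said is that the article neither includes nor excludes the strata. Their contribution may in any case be small: the Concomitant treatments and procedures section lists a glycoprotein IIb/IIIa inhibitor among the treatments that all patients are to receive, and if that is followed the stratum hardly varies.

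Nor does the document show that baseline hsCRP is strongly prognostic. Patients entering at different points of a curve that rises and then falls could show a weak relation: an early presenter may start low and go on to a large AUC. At r = 0.2 the gain is only about 1.5 power points. This is why the range starts low and no single value is claimed.

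What the reply does not answer is that the named method, as worded, has no place for a continuous baseline term that is already scheduled and costs nothing to use.

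**Conclusion.** The point holds as a free improvement in precision together with a gap in specification. The stated analysis is valid and reaches about 81% power at 0.45 SD. Adjusting for log baseline hsCRP would raise this to between 82.5% and 98% for r between 0.2 and 0.7, equal to an unadjusted trial of about 173 to 325 evaluable patients instead of 166. The size rests on r, which the document does not give, and on 83 evaluable patients per arm, a two-sided final alpha of 0.045 and a true difference of 0.45 SD. The gain from the strata is probably smaller and depends on how much variance they explain, which is also not given. If the AUC itself includes the baseline reading, which the text leaves unclear, part of the correlation is built in; adjustment remains valid.

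**What to change.** Before unblinding, and for the interim and final analyses alike, specify the primary model as an ANCOVA of log 7-day hsCRP AUC on treatment, log baseline (pre-dose) hsCRP, centre and GP IIb/IIIa stratum. Report the treatment effect as a geometric mean ratio with its confidence interval. Keep the unadjusted ANOVA as a sensitivity analysis.

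Time from symptom onset should not be a required covariate: the eligibility criteria use a 48-hour limit, but the document does not show that the interval is recorded as a variable.

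The cost is a sentence or two of protocol or analysis-plan wording. No patients, visits or assays are added, since baseline hsCRP is already scheduled and both strata are known at randomisation. Fixing the terms in advance also removes any choice of model after the data are seen.

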In the latter group (markers of the pathological process) are the markers of inflammation, coagulation and of platelet activation. We believe that there are plausible links between IL-1 activation and these markers. The acute phase reactant C-reactive protein (CRP) is a strong predictor of cardiovascular events [27,28]. In NSTEMI ACS, treated with percutaneous coronary intervention (PCI), CRP rises and peaks between 24 and 48 hours [29]. It is clear, however, that in some patients there is persistent elevation with maybe 49% of patients having a CRP >3 mg/L at discharge and these patients were identified as having increased chances of recurrent admissions [30]. The absolute levels of CRP have been shown to have a high sensitivity (87%) and a low specificity (54%) for subsequent myocardial infarction in patients presenting with an ACS [31]. There is a difficulty using a percentage change in CRP, either for individual patients and predicting outcome or between two groups of (treated) patients, in that there is no baseline level from which comparisons can be made. Differences in outcomes in the PROVE-IT trial, however, were associated with differences in the achieved CRP level [23,32]. Biologically, CRP production by hepatocytes has to be induced and this has been shown to be driven by the IL-1 and IL-6 cytokines. Serum levels of IL-6 have been shown to be elevated in patients with ACS [33] and an elevation of IL-6 is an independent marker of increased mortality in ACS [30]. The relationship between IL-1 and IL-6 is well defined with IL-1 inducing IL-6 production [7]. It has, however, proved difficult to reliably measure IL-1β; a cytokine that is devoid of a signal sequence directing release and which probably circulates at a very low level.

During NSTEMI, a rise in von Willebrand Factor (vWF) between 24 and 48 h predicts adverse clinical events [18], and an association between circulating levels of IL-6 and von Willebrand factor (vWF) has recently been shown to determine prognosis in patients with ACS [34]. IL-1 has been shown to augment thrombin-induced release of vWF from human endothelial cells [35].

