### Outcome measures

#### Primary outcome measure (comparison of treatment group with control)

Area under the curve of serum high sensitivity CRP over the first 7 days

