#### Drug related adverse reactions

In all placebo-controlled trials conducted by Amgen, injection site reactions (ISRs) were frequently reported in the majority of patients (95% of which were reported to be mild to moderate in severity). ISRs included erythema, ecchymosis, inflammation and pain. On a dose of 100 mg/day, 71% of patients developed an ISR (n = 1565) compared to 28% of placebo treated patients (n = 733). The median duration of typical symptoms was 14 to 28 days. Other adverse events reported by patients administered with IL-1ra were, URI, headache, nausea, diarrhoea, sinusitis, arthralgia, flu like symptoms and abdominal pain. Allergic reactions reported in patients were rare.

Reported ISRs and other drug related adverse reactions will be reported on the adverse event report in the CRF. Patients reporting ISRs will be required to identify another injection site in which to administer the injection. Investigators will submit all adverse events reports for each patient to the CTEU at days 7, 14 and 30, three months and one year. The CTEU will maintain a log of all adverse reactions.

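### Last observation carried forward misstates the 7-day hsCRP AUC of patients with missing readings; bias in the treatment comparison is possible but not established

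*Protocol article*

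**What the plan says.** The primary outcome is given as "Area under the curve of serum high sensitivity CRP over the first 7 days", and the Primary analysis section adds: "Primary analysis will be of log-transformed AUC of 7 day CRP". On who is analysed: "The primary analysis will include all patients with at least 4 follow-up readings, on an intention-to-treat basis". For those patients, "any missing measurements will be imputed using the last observation carried forward method". No reason is given for the choice.

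Sampling is at baseline, daily on Days 1–7, and on Days 14 and 30 (Study related investigations and follow-up). For patients who go home early, "If the patient is discharged before the seventh day, they will be required to attend clinic" for the remaining samples.

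On the expected course of the marker, Markers of inflammation in ACS says: "In NSTEMI ACS, treated with percutaneous coronary intervention (PCI), CRP rises and peaks between 24 and 48 hours". The same paragraph adds that CRP stays raised in some patients.

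The only other analysis of this outcome is a per-protocol analysis of patients with every reading.

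**The concern.** Carrying the last value forward assumes that CRP does not change after the last reading. The article's own account is of a marker that climbs, peaks early and, apart from the patients who stay raised, comes down. The primary endpoint integrates the daily values, so each frozen value enters it directly.

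Reading the 4-reading rule as applying to Days 1–7, up to 3 of the 7 daily values can be filled this way. A patient who simply stops attending then has a last reading on Day 4 or later, normally after the stated peak. Late gaps are the more likely ones, because sampling after discharge needs a clinic visit. For an internal gap the rule also ignores a later observed value. At stake are the accuracy of the primary endpoint in affected patients and, if the pattern differs by arm, the estimated treatment effect.

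**Working it through.** **1. The plan's own figures.** Inputs from Sample size: standardised difference 0.45, 80% power, 5% significance (taken as two-sided), 1:1 allocation.

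- n per group = 2(1.96 + 0.84)²/0.45² ≈ 78, against about 80 stated. Power at 80 per group is 81.2%.
- 160/(1 − 0.10) = 178, against about 180 stated.

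Both reproduce. The article gives no figure for the effect of carry-forward, so everything below rests on assumed curves and assumed missingness.

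**2. One illustrative patient.** Assumed hsCRP, baseline to Day 7: 5, 12, 20, 16, 12, 9, 7, 5.5 mg/L. Trapezoidal AUC = (first + last)/2 + sum of the values between.

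- Complete: 5.25 + 76 = 81.25.
- Days 5–7 missing, 12 carried forward: 8.5 + 84 = 92.5, or +14%.
- Days 4–6 missing, Day 7 observed, 16 carried forward: 5.25 + 96 = 101.25, or +25%.
- The same gap, linear interpolation (13.375, 10.75, 8.125): 5.25 + 48 + 32.25 = 85.5, or +5%.

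**3. A range of curves.** Assumed profile, as a fraction of peak:

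- up to peak day p: y(t) = 0.4 + 0.6t/p
- after it: y(t) = f + (1 − f)·0.5^((t − p)/h)

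with p = 1 or 2, floor f = 0 or 0.2, and half-life h = 1, 1.5, 2, 3 or 4 days. Example (p = 2, f = 0, h = 2): complete AUC 3.799, carried forward from Day 4 4.357, ratio 1.147.

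| Readings missing | Error in AUC, carry-forward | Linear interpolation |
|---|---|---|
| Days 5–7 (last reading Day 4) | +5.5% to +15.8% | – |
| Days 6–7 (last reading Day 5) | +1.4% to +5.1% | – |
| Day 7 (last reading Day 6) | +0.2% to +1.0% | – |
| Days 3–5 (internal gap) | +12% to +75% | +1.5% to +25% |
| Days 1–3 (baseline carried) | −25% to −35% | – |

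**4. The treatment comparison.** Let s = ln(carry-forward AUC/complete AUC) in an affected patient, and m the proportion affected. Then

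estimated log ratio = ln(2/3) + m(active)·s(active) − m(placebo)·s(placebo).

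The true ratio is set at 0.667, the article's one-third reduction. The log-scale SD is taken as ln(1.5)/0.45 = 0.90, implied by the sample-size text but not stated there. Other settings: last reading Day 4, p = 2, f = 0, h = 1.5 to 3, 80 per group.

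| Days 5–7 missing | Estimated ratio | Power |
|---|---|---|
| 10%, 20% or 30% in both arms, proportional curves | 0.667 | 81% |
| 10–30% in both arms, half-life halved on active | 0.660–0.674 | 79–83% |
| 30% active v 10% placebo, proportional curves | 0.682–0.687 | 75–77% |
| 10% active v 30% placebo, proportional curves | 0.647–0.652 | 85–86% |

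Example for the third row, h = 1.5: s = ln(1.158) = 0.147; shift = (0.30 − 0.10) × 0.147 = 0.029; exp(−0.405 + 0.029) = 0.687.

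For a drug with no effect, the same 0.029 is 0.029/0.90 = 0.03 SD. With 80 per group that moves a nominal two-sided 5% error rate to about 5.5%.

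**5. Equal missingness, effect building over time.** The article puts the CRP reduction in rheumatoid arthritis at about a week of treatment. On the curve in step 2, assume an active/placebo ratio falling linearly from 1.0 at baseline to 0.65 at Day 7. The AUC ratio is 68.54/81.25 = 0.844 complete and 79.1/92.5 = 0.855 with Day 4 carried forward, about 8% less log effect in affected patients. With 10–30% affected in both arms, overall attenuation is about 1–2.5%.

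**The case against.** The strongest reply is that the quantity of interest is the difference between arms, and errors common to both arms cancel on the log scale. Step 4 bears this out. The article expects almost all follow-up to be obtained and allows 10% data loss equally in each arm. The 4-reading rule keeps most patients who stop sampling in the 0–5% range; the 14% and 25% figures need the minimum number of readings. The 24–48 hour peak is stated for PCI-treated patients, its time origin is not given, and patients with persistent elevation would be overstated less. The analysis of patients with complete readings involves no imputation.

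Most of this stands as a limit on size. It does not justify the rule. The complete-readings analysis is per-protocol, so it changes the population and cannot show what imputation did within the intention-to-treat set.

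A reader might infer that the primary treatment comparison is biased, and against the drug, because injection-site reactions differ: "71% of patients developed an ISR (n = 1565) compared to 28% of placebo treated patients". The article does not support that. It describes 95% of these reactions as mild to moderate, deals with them by changing the injection site, and does not link them to missed blood samples. The 30% v 10% split is an assumption, and reversing it reverses the bias. Single imputation also treats filled values as observed, but with one log AUC per patient its effect on the standard error was not quantified and should not be pressed.

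**Conclusion.** The point holds as a defect in the imputation rule. Carry-forward does not fit a marker that the article describes as peaking early, and it misstates AUC in affected patients: typically upward for readings lost after the peak, downward for readings lost on the rise. The sizes are those in step 3 and depend on assumed decay rates.

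Material bias in the treatment effect is not shown. It needs missingness or CRP time course to differ by arm, and neither the pattern nor the direction can be fixed from the article. Even at 30% v 10% the shift is only about 0.02–0.03 on the log scale, against a design effect of 0.405. This should be fixed because the better method is cheap and the endpoint is the only primary one; it does not invalidate the trial.

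**What to change.** Replace the carry-forward sentence in Primary analysis, before unblinding, along these lines:

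- Compute AUC by the trapezoidal rule on actual sampling times, so that internal gaps are interpolated between observed values. Step 3 shows that this is much closer than carry-forward but not exact for a three-day gap just after the peak; such gaps could go into the imputation below.
- For trailing gaps, multiply impute log hsCRP within arm from baseline, all observed days and the already scheduled Day 14 value; derive log AUC in each completed data set and combine by Rubin's rules.
- A repeated-measures model of log hsCRP is an alternative. It averages daily logs rather than taking the log of the AUC, so multiple imputation keeps closer to the stated endpoint.
- Keep carry-forward only as a sensitivity analysis in the same intention-to-treat set.

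The cost is revised wording and a little more programming, with no new data. The new method rests on a missing-at-random assumption, which should be stated.
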